| QoL (SF-36 / FACIT-F)                               |                                                                                           | X                          |                                |                                |                            |                            |                                         |                           |                            |                            |                             |                             |                                 |                                 |                                 | X                                        |
| Sjogrens assessments                    |                                                                                           | X                          |                                |                                |                            |                            |                                         |                           |                            |                            |                             |                             |                                 |                                 |                                 | X                                        |
| hsCRP, ESR                              | X                                                                                         | X                          |                                |                                |                            | X                          |                                         | X                         | X                          |                            | X                           |                             |                                 |                                 |                                 | X                                        |

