| Monitoring of adverse events                     | MONITOR AND RECORD THROUGHOUT THE STUDY AS PER INSTRUCTIONS IN SECTION 15.2 |                                       |                                                   |
| Monitoring of concomitant therapy                | MONITOR AND RECORD THROUGHOUT THE STUDY AS PER INSTRUCTIONS IN SECTION 15.2 |                                       |                                                   |

CONFIDENTIAL

The information contained herein may not be used, disclosed, or published without the written consent of Biogen Idec Inc.

Vital signs include temperature, heart rate, respiratory rate, and blood pressure. Blood pressure to be performed supine after 5 minutes rest.

Measurements include: swollen and tender joint counts (66/68), subject/Investigator global assessment of disease activity, HAQ-DI, and subject's assessment of pain (VAS)

Assessments include: subject-reported dryness including VAS (ocular, vaginal, skin, and oral) and OSDI. To be conducted in subjects with Sjogrens syndrome only.

ESR to be performed at local laboratory.

RA disease markers include: serum BAFF, COMP, calgranulin, and MMP3.

**Only to be taken from subjects participating in the optional PK sub-study.**

PPD test to be read 48-72 hours after planting.

Not required if performed within 3 months prior to Day 0 and was without clinically significant abnormality. However, if PPD induration is  $\geq 5$  mm, but  $< 10$  mm (size of raised bump, not redness), a chest X-ray is required, regardless of when the last X-ray was taken.

Only to be taken from subjects with positive ANA/anti-dsDNA at Week 14.

a**Visit only applicable to subjects participating in the optional PK sub-study. Subjects will sign a separate informed consent form.**

bOption to enter safety data extension study. If subject withdraws from the study prior to Visit 9/Week 14, all Week 14 assessments should be completed at the withdrawal visit.

cIf subject withdraws from the study during the post-treatment period, Week 26 assessments should be completed at the withdrawal visit.

---

CONFIDENTIAL

The information contained herein may not be used, disclosed, or published without the written consent of  
Biogen Idec Inc.

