#### **14.2.16 Visit 12 (Week 26, Day 182 ±3; late withdrawal visit [withdrawal after Week 14])**

- Physical examination
- Vital signs: temperature, heart rate, respiratory rate, and supine blood pressure (after 5 minutes' rest)
- ACR core set measurements (see Section 12.1 for list of measurements)
- QoL (SF-36, FACIT-F)
- Sjogrens assessments (see Section 12.1 for assessments), if applicable
- Blood samples collected for:
  - hsCRP and ESR (ESR to be performed at local laboratory)
  - Serum BG9924 PK concentration
  - Hematology (see Section 13.2 for list of variables)
  - Quantitative Ig (IgA, IgG, and IgM)
  - Blood chemistry (see Section 13.2 for list of variables)
  - INR, PT, and aPTT
  - ANA and anti-dsDNA antibody assays (only from subjects with positive ANA/anti-dsDNA at Week 14)
  - Serum anti-BG9924 antibody assay
  - Tetanus antibody titers
- Urinalysis (see Section 13.2 for list of variables)
- Monitoring of AEs/SAEs (see Section 15.2)

- Monitoring of concomitant therapy

Visit 12 (Week 26) evaluations will be completed for all subjects who complete the treatment and post-treatment period, or who withdraw during the post-treatment period.

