## **16.2 Criteria for the Endpoints**

All statistical tests will be 2-sided with a type I error rate of 5%. Formal statistical comparisons for efficacy endpoints will be made between each BG9924 dose group versus placebo. No adjustments will be made for multiple comparisons.

Subjects with missing efficacy measurements at the visit being analyzed will be considered treatment failures for that visit. Subjects who require rescue interventions (Section 11.4) will be considered a non-responder for all analysis time points subsequent to usage of the rescue medication. Missing values for continuous endpoint values will be replaced using last observation carried forward (LOCF).

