##### Secondary endpoints:

##### Proportion of subjects with an ACR20 and ACR70 at Week 14

The endpoints, ACR20 and ACR70 at Week 14, will be analyzed using a chi-square test, Fisher's exact test, or logistic regression with treatment group as a term in the model, as appropriate.

##### Change from baseline in Quality of Life (HAQ-DI, SF-36, FACIT-F) at Week 14

Change from baseline for HAQ-DI, FACIT-F scores, and SF-36 scores (mental and physical health components) will be analyzed using an analysis of covariance with treatment group and baseline as terms in the model. If the data are not normally distributed, a nonparametric analysis of covariance will be performed.

##### Change from baseline disease activity score (DAS28) at Week 14

The DAS28 score is a measure of the subject's disease activity and is calculated as follows:

$$\text{DAS28} = 0.56 * \text{sqrt}(\text{TJC } 28) + 0.28 * \text{sqrt}(\text{SJC } 28) + 0.70 * \ln(\text{ESR}) + 0.014 * \text{GH}$$

(TJC = tender joint count; SJC = swollen joint count; ESR = erythrocyte sedimentation rate; GH = subject's global assessment)

and/or

$$\text{DAS28} = 0.56 * \text{sqrt}(\text{TJC } 28) + 0.28 * \text{sqrt}(\text{SJC } 28) + 0.36 * \ln(\text{CRP}+1) + 0.014 * \text{GH} + 0.96$$

Change from baseline disease activity score (DAS28) will be analyzed using an analysis of covariance with treatment group and baseline as terms in the model. If the data are not normally distributed, a nonparametric analysis of covariance will be performed.

##### Proportion of subjects with a categorical DAS28 EULAR response at Week 14

The EULAR response categories of good, moderate, and no response are defined as shown in Table 16-1 below.

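### LOCF as the main rule for all continuous endpoints risks bias in either direction in the Week 14 DAS28, HAQ-DI, SF-36 and FACIT-F comparisons, and becomes baseline carried forward for SF-36 and FACIT-F in subjects with no withdrawal-visit score

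*Protocol*

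**What the plan says.** Section 16.2 has two missing-data rules. For responder endpoints, "Subjects with missing efficacy measurements at the visit being analyzed will be considered treatment failures for that visit". For the rest, "Missing values for continuous endpoint values will be replaced using last observation carried forward (LOCF", with no exception by endpoint.

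Section 16.2.4.2 then tests the continuous secondary endpoints at Week 14. For quality of life: "Change from baseline for HAQ-DI, FACIT-F scores, and SF-36 scores (mental and physical health components) will be analyzed using an analysis of covariance". For DAS28: "Change from baseline disease activity score (DAS28) will be analyzed using an analysis of covariance". In both cases the terms are treatment group and baseline. Individual ACR core set changes are only summarised.

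The schedule differs by endpoint. In the Section 4 table, the row "QoL (SF-36 / FACIT-F" is marked in the treatment period and at Week 14 only for Visit 1 (Day 0) and Visit 9 (Week 14). Sections 14.2.2 and 14.2.13 agree. The next assessment is at Week 26 (Section 14.2.16), after the analysis point. HAQ-DI belongs to the core set, whose footnote reads "Measurements include: swollen and tender joint counts (66/68), subject/Investigator global assessment of disease activity, HAQ-DI, and subject's assessment of pain (VAS". The core set, hsCRP and ESR are taken at Screening and at Weeks 0, 2, 4, 6, 10 and 14.

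A footnote to the Section 4 table and Section 14.2.13 ask for all Week 14 assessments at an early-withdrawal visit. Section 11.2.2 says only that such subjects should be encouraged to complete them if possible.

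**The concern.** LOCF assumes that a subject who leaves would have stayed at the last recorded value until Week 14. If response builds over the 14 weeks, dropouts are frozen at an earlier and usually smaller change. If the share of dropouts differs between arms, the arms are frozen to different degrees, and part of the estimated difference reflects dropout and not the drug.

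The problem is sharper for SF-36 and FACIT-F, because there is no on-treatment score to carry unless a withdrawal visit took place.

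At stake are the formal comparisons of each of five regimens with placebo on four secondary measures, in a trial meant to help choose a dose.

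**Working it through.** **What the plan's own figures cover.** The only power statement (Section 16.4) concerns ACR50 and gives 90% and 74%. With 15% dropout, 42% against 15%, and Fisher's exact test, enumeration gives 90.6% for 64 against 64. For 32 against 64 it gives 74.9% if the two-sided p-value is twice the one-sided one. Both figures reproduce. They do not involve LOCF.

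**Number exposed.** Section 16.4 assumes 15% dropout: 0.15 × 76 = 11.4 subjects per every-other-week or placebo group and 0.15 × 38 = 5.7 per monthly group.

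**SF-36 and FACIT-F.** Let m be the mean Week 14 change in SD units, d the dropout share, and f the share of dropouts with no withdrawal-visit score. A and P denote active and placebo. If dropout is unrelated to outcome, the expected difference is

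(1 − f·dA)·mA − (1 − f·dP)·mP

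Assume mA = 0.7 and mP = 0.3, a true difference of 0.40.

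| Dropout active / placebo | f | Calculation | Result |
|---|---|---|---|
| 15% / 15% | 1 | 0.85 × 0.7 − 0.85 × 0.3 | 0.34 (15% smaller) |
| 15% / 15% | 0.5 | 0.925 × 0.7 − 0.925 × 0.3 | 0.37 (7.5% smaller) |
| 25% / 5% | 1 | 0.75 × 0.7 − 0.95 × 0.3 | 0.24 |
| 5% / 25% | 1 | 0.95 × 0.7 − 0.75 × 0.3 | 0.44 (inflated) |

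The rows with f = 1 assume no withdrawal-visit scores. The row with f = 0.5 credits such scores with the full Week 14 change. If they come earlier on a rising course, the shrinkage lies between 7.5% and 15%.

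**DAS28.** Assume a placebo improvement of 0.80, an active improvement of 1.60 (effect -0.80), and dropouts spread evenly over last observations at Weeks 0, 2, 4, 6 and 10. With linear onset the carried value holds on average

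k = (0 + 2 + 4 + 6 + 10) / (5 × 14) = 0.314

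of the Week 14 change. Each arm's mean change is multiplied by 1 − d + d·k.

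- 15% / 15%: 0.80 × (0.85 + 0.15 × 0.314) = 0.80 × 0.897, so the effect is -0.72.
- 20% active / 10% placebo: 1.60 × 0.863 − 0.80 × 0.931 = 1.381 − 0.745, so -0.64.
- 5% active / 25% placebo: 1.60 × 0.966 − 0.80 × 0.829 = 1.545 − 0.663, so -0.88, an exaggeration.
- Early onset (half the effect at Week 2, all from Week 4): k = (0 + 0.5 + 1 + 1 + 1) / 5 = 0.70. With 15% / 15%, 0.80 × 0.955, so -0.76.

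Simulation (76 per arm, SD 1.3, within-subject correlation 0.6, ANCOVA after LOCF) gives the same values to within 0.01.

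**No true effect.** With a common improvement c, linear onset and 20% active / 10% placebo dropout, the bias is c × 0.10 × (1 − 0.314), against active treatment. The standard error is about 1.3 × √(1 − 0.36) × √(2/76) = 0.169. For c = 0.8 the bias is 0.055 and two-sided rejection about 6.2%. For c = 1.2 it is 0.082 and about 7.8%. Simulations gave 6.3% to 8.4% over a range of c. With equal dropout, rejection stays near 5%.

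**The case against.** **The withdrawal visit.** A reader might infer that for SF-36 and FACIT-F the rule simply is baseline carried forward. The documents do not support that. The withdrawal visit collects both questionnaires, and Section 11.2.1 asks that subjects who stop treatment be encouraged to attend from Week 14 on. Zero change is imputed only where neither assessment exists. What remains is that attendance is encouraged and not assured, and that a withdrawal score is still an earlier score labelled Week 14.

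**Certainty and direction.** A reader might also infer that bias is certain, or always towards no effect. Neither holds. Equal dropout unrelated to outcome, with no drug effect, gives none, and the sign turns on which arm loses more subjects. Section 5.1.1 reports joint-count improvement after 4 weeks, and Section 5.4 gives the loading dose partly for a possibly faster response. Both favour early onset and a smaller loss for DAS28 and HAQ-DI. In the 20% / 10% null case the excess rejections fall mostly on the side of placebo, so they are not mainly false efficacy claims.

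**Standard error.** One might argue that counting 76 values when about 65 were observed understates the standard error by 7%, from √(65/76) = 0.925. That does not follow. Each subject still contributes one independent value, and the residual variance is estimated from the values analysed. Under baseline carried forward with 15% dropout in both arms, the simulated model standard error was 0.163 against an empirical SD of 0.165.

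**Scope.** ACR50, ACR20 and ACR70 use failure imputation. No section ties dose selection to these secondary endpoints, so it cannot be said that dose selection is distorted, only that evidence bearing on it may be. Missing-at-random is also untestable, and sensitivity analyses may sit in an SAP not shown. The main rule, however, is fixed in the protocol.

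**Conclusion.** The point holds as a risk to the continuous secondary endpoints. LOCF is the stated main rule and cannot be defended as conservative, because the bias can go either way. For SF-36 and FACIT-F it gives zero change to subjects with neither a Week 14 nor a withdrawal assessment.

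Plausible sizes are a loss of about 5% to 10% of a DAS28 effect with equal 15% dropout (-0.80 to -0.76 or -0.72), and about 20% with 20% active / 10% placebo dropout and linear onset (-0.64). SF-36 and FACIT-F effects shrink by up to 15%, or about half that if half the dropouts have a withdrawal score. With no effect and 20% / 10% dropout, rejection is roughly 6% to 8%. All rest on assumed SDs, time courses, mean changes and arm-specific dropout. Only the 15% overall dropout and the group sizes come from the protocol.

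The primary endpoint and its power are untouched. The change is advisable, not essential to the trial's main result.

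**What to change.** In Section 16.2, replace LOCF as the main rule for the tested continuous endpoints.

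- **DAS28 and HAQ-DI:** a mixed model for repeated measures on all scheduled visits, with treatment-by-visit, baseline-by-visit and the anti-CCP-2 stratum used in randomisation (Section 9.2), reporting the Week 14 contrast of each regimen with placebo.
- **SF-36 and FACIT-F:** the planned ANCOVA after multiple imputation, with the repeatedly measured HAQ-DI, pain and global scores as auxiliary variables.
- Keep LOCF as a sensitivity analysis, and leave individual core set changes descriptive.

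The cost is a few sentences in Section 16.2, matching wording in Section 16.2.4.2 and slightly more programming. No new visits or data are needed. The downside is reliance on missing-at-random, which the data cannot verify.

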### **16.2.1 Demography and Baseline Disease Characteristics**

Demographics and baseline data will be summarized for each treatment group by presenting basic summary statistics (mean, standard deviation, median, and range) and/or frequency distributions.

### **16.2.2 Pharmacokinetics**

#### **16.2.2.1 Analysis Population**

The PK population will be defined as all subjects who received at least one dose of study treatment and have at least one measurable drug concentration.

#### **16.2.2.2 Methods of Analysis**

A population PK approach will be taken to determine the PK behavior of BG9924. A PK compartmental model that best describes the drug concentration vs. time data will be determined using the concentration, dose, and times of drug administration and sampling as the parameters that distinguish the model. Typical PK parameters needed to describe these data, including volume of distribution (V) and clearance (Cl), will be determined. Secondary parameters, including half-life and area under the curve (AUC), will also be reported. The maximum concentrations ( $C_{\max}$ ) and times to maximum concentrations ( $t_{\max}$ ) will be documented. Parameter estimates for the compartmental modeling will be generated for each subject using a post-hoc estimation method.

A subpopulation of subjects will have additional samples collected to provide a more definitive basis for the proper PK compartmental model. This basis of definition will be used to describe BG9924 disposition in all study subjects.

The PK will be evaluated for the possible influence of factors that may influence the disposition of BG9924. This would include, but is not limited to, subject demographics, laboratory tests indicative of hepatic or renal function, and presence of anti-drug antibodies.

#### **16.2.3 Pharmacodynamics**

##### **16.2.3.1 Analysis Population**

The pharmacodynamics population will be defined as all subjects who received at least one dose of study treatment and have an adequate number of biomarker data points.

##### **16.2.3.2 Methods of Analysis**

Pharmacodynamic measurements, including disease markers, as well as markers for drug activity, will be reviewed for the existence of patterns with time and drug exposure. If applicable, the maximum or minimum values and times to achieve those maximum and minimum values will be documented and reported.

Summary statistics and graphical presentations will be presented for each pharmacodynamic assessment, as appropriate.

#### **16.2.4 Efficacy Data**

##### **16.2.4.1 Analysis Population**

The efficacy population will be defined as all subjects who received at least one dose of study treatment. Additional analyses may be performed on subjects compliant with the dosing regimen.

#### **16.2.4.2 Methods of Analysis**

##### Primary endpoint: Proportion of subjects with an ACR50

The primary endpoint will be analyzed using a chi-square test, Fisher's exact test, or logistic regression with treatment group as a term in the model, as appropriate.

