### **9.2 Randomization Procedures**

Subjects will be randomized after the Investigator has verified that they are eligible per criteria in Section 8.1 and Section 8.2. Randomization will be stratified by screening anti-CCP-2 status. Subjects will be randomized to receive placebo or BG9924 (1 of 5 dosing regimens) in a 2:2:2:2:1:1 ratio. Subjects withdrawn from the study may possibly be replaced.

Randomization will take place across all study sites using a centralized Interactive Voice Response System (IVRS; see Section 19.1.1). At randomization, the IVRS will assign a unique 6-digit subject identification number to each subject (the first segment of the number represents the study site and the second segment of the number represents the subject at that study site). The subject's identification number will be used on all of that subject's Case Report Forms (CRFs), test results, etc.

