### **16.4 Sample Size Considerations**

A total of 380 subjects will be randomized at a ratio of 2:2:2:2:1:1 providing 76 subjects per treatment group for every other week dosing and 38 subjects per treatment group for monthly dosing. Assuming 15% dropout, a Type I error rate of 5%, Week 14 ACR50

CONFIDENTIAL

The information contained herein may not be used, disclosed, or published without the written consent of  
Biogen Idec Inc.

responses of a single BG9924 treatment group (42%) and placebo (15%), there is 90% power for a comparison of an every other week BG9924 treatment group versus placebo and 74% power for a comparison of a monthly BG9924 treatment group versus placebo by using Fisher's exact test.

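### Randomization is stratified by anti-CCP-2 status, but no stated efficacy model uses that factor, and the primary ACR50 test is an unfixed choice among three

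*Protocol*

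**What the plan says.** Protocol Section 9.2: "Randomization will be stratified by screening anti-CCP-2 status". No other stratification factor is named.

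Protocol Section 16.2.4.2 gives the primary ACR50 analysis as a chi-square test, Fisher's exact test, "or logistic regression with treatment group as a term in the model, as appropriate". ACR20, ACR70 and EULAR response get the same three options. Change in HAQ-DI, SF-36, FACIT-F and DAS28 "will be analyzed using an analysis of covariance with treatment group and baseline as terms in the model", with a nonparametric version if the data are not normal. The synopsis repeats these methods. Anti-CCP-2 status appears in none of them.

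Section 16.2 sets two-sided tests at 5% and adds: "Formal statistical comparisons for efficacy endpoints will be made between each BG9924 dose group versus placebo". It makes no multiplicity adjustment and counts subjects with missing efficacy measurements as treatment failures.

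Section 16.4 bases power on Fisher's exact test, but does not say that this is the test to be used for the primary analysis.

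**The concern.** There are two separate points.

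1. **Design and analysis do not match.** The sponsor chose anti-CCP-2 status as the one factor to balance on. The usual reason is an expectation that it bears on response. If it does, an analysis that ignores it treats the balance as chance and slightly overstates the standard error.
2. **The primary decision rule is not fixed.** Three tests are permitted, and they do not always agree at 76 or 38 subjects per arm. With five regimens each compared with placebo at an unadjusted 5%, this adds discretion to a set of comparisons that already lacks familywise control. A reader of the final report could not tell from the protocol which p-value was meant to count.

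**Working it through.** **Inputs from the protocol.** Section 16.4: 380 subjects at 2:2:2:2:1:1, so 76 on placebo and in each every-other-week arm and 38 in each monthly arm; ACR50 42% against 15%; 15% dropout; Fisher's exact test. Section 16.2: two-sided 5%, missing counts as failure.

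**Step 1. The plan's own power.** Removing 15% leaves 76 × 0.85 = 64.6 and 38 × 0.85 = 32.3 per arm. Exact enumeration of the two binomials at 42% against 15%, using Fisher's test with the one-sided p doubled:

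| Comparison | n | Power | Stated |
|---|---|---|---|
| Every other week v placebo | 64 v 64 / 65 v 65 | 90.6% / 91.1% | 90% |
| Monthly v placebo | 32 v 64 / 32 v 65 | 74.9% / 74.2% | 74% |

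The stated figures are reproduced. They also hold when dropouts stay in the denominator as failures. The rates become 0.85 × 42% = 35.7% and 0.85 × 15% = 12.75%, and power is 89.4% (76 v 76) and 73.9% (38 v 76).

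**Step 2. Can the choice of test change the result?** Take 21/76 against 11/76. The pooled rate is 32/152 = 0.2105, and

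z = (p1 − p2) / √[p(1 − p)(1/n1 + 1/n2)] = (0.2763 − 0.1447) / 0.0661 = 1.99,

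so chi-square gives p=0.047. Fisher's exact test on the same table gives p=0.072. Other tables that flip:

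| Table | Fisher | Chi-square | Logistic (Wald) |
|---|---|---|---|
| 23/76 v 12/76 | 0.053 | 0.034 | 0.037 |
| 20/76 v 10/76 | 0.066 | 0.042 | 0.045 |
| 11/38 v 10/76 | 0.070 | 0.040 | 0.045 |

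**Step 3. How often?** Exact enumeration at 35.7% against 12.75%:

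| n | Fisher power | Chi-square power | Trials in which they disagree |
|---|---|---|---|
| 76 v 76 | 89.4% | 92.4% | 3.0% |
| 38 v 76 | 76.7% | 80.2% | 3.6% |

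Here Fisher's two-sided p is the probability-ordered one. With the doubled p, Fisher's power at 38 v 76 is 73.9%, so the gap to chi-square is 80.2 − 73.9 = 6.3 points. At an assumed smaller effect of 30% against 15% with 76 v 76, the two tests disagree in about 7% of trials. With no effect (15% in both arms, 76 v 76) they disagree in 2.2%.

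**Step 4. Type I error if the most favourable of the three tests were always taken.** At 15% in both arms it is about 0.051 for 76 v 76 and up to 0.057 for 38 v 76. Fisher alone gives 0.029 to 0.034.

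**Step 5. What does the missing stratum cost?** The protocol gives neither the share of anti-CCP-2 positive subjects nor the link between anti-CCP-2 status and ACR50. Assumed: 60 to 80% positive; odds ratio for response from 1/3 to 5; a common treatment odds ratio across strata. Simulation (200,000 runs per scenario) at 42% against 15%:

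| n | Unstratified chi-square | Stratified Cochran-Mantel-Haenszel (CMH) | Difference (points) |
|---|---|---|---|
| 65 v 65 | 94.1–94.9% | 93.8–95.7% | −0.3 to +0.8 |
| 32 v 65 | 82.3–84.7% | 82.4–85.7% | −0.5 to +2.5 |

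Type I error at 15% in both arms is 0.042 to 0.048 unstratified and 0.046 to 0.052 stratified. With full arms of 76, dropouts as failures and 70% positive, stratified against unstratified power is 92.3% v 92.3% (odds ratio 1), 92.7% v 92.5% (odds ratio 2) and 93.5% v 92.9% (odds ratio 4).

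**The case against.** The other side has several good arguments.

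- **Lost power.** A reader might infer that leaving out the stratum wastes appreciable power. The documents do not support that: they say nothing about how anti-CCP-2 status predicts ACR50, and over a wide assumed range the effect is small and can be slightly negative. Comparing Fisher (89.4%) with a stratified test would credit stratification with a gain that an unstratified chi-square (92.4%), already permitted by Section 16.2.4.2, delivers alone. This objection stands.
- **Sample size and validity.** Power was computed with the most conservative of the listed tests and is reproduced. Omitting the stratum makes the test mildly conservative; it does not inflate type I error. This also stands.
- **Choice after unblinding.** A reader might infer that the test will be picked once results are known. Nothing in the protocol says so. The point is only that the protocol does not fix the choice.
- **The flip is uncommon.** At the planned effect about 96 to 97% of trials give the same answer by Fisher and chi-square, and this is a dose-finding study, where one arm's p-value near 0.05 should not decide everything. This limits the severity.
- **It belongs in the statistical analysis plan.** That plan is not shown and may settle both points. Also, naming treatment as a term does not literally exclude others. This stands only in part. The protocol does not stay silent: it states model terms, those for the analyses of covariance read as a complete list, and it states the primary test as an open menu. As written, they do not match the protocol's own randomization.

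**Conclusion.** The point holds as a mismatch between design and analysis and as an unfixed primary test, not as a power deficit or a threat to validity. Fisher and chi-square fall on opposite sides of 0.05 in about 3 to 4% of trials at the planned effect, per comparison (probability-ordered Fisher; for monthly arms the gap is about 6 points if the p-value is doubled). At an assumed 30% against 15% with 76 v 76 the figure is about 7%. The stratum itself is worth −0.3 to +0.8 points of power for every-other-week arms and −0.5 to +2.5 for monthly arms; these ranges rest on the assumed prevalence and odds ratios, which the protocol does not give. The stated 90% and 74% need no change. Severity is minor to moderate.

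**What to change.** In Section 16.2.4.2 and the synopsis:

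1. Name one primary test for each BG9924 arm against placebo that uses the randomization stratum, for example CMH stratified by screening anti-CCP-2 status, or logistic regression with treatment and anti-CCP-2 status as terms.
2. Use the same test for ACR20, ACR70 and EULAR response.
3. Add the anti-CCP-2 stratum to the analyses of covariance for HAQ-DI, SF-36, FACIT-F and DAS28, including the nonparametric version.
4. Keep unstratified Fisher's exact test as a sensitivity analysis, which also links the result to the power calculation in Section 16.4.

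CMH is one choice among several. Naming any single listed test would remove the ambiguity; using the stratum also brings the analysis into line with the randomization. The cost is a few sentences, settled before unblinding. It needs no extra subjects, visits or data, because screening anti-CCP-2 status is already collected to stratify the randomization.
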